## Methods

### Study objectives

#### Primary objective

This study aims to evaluate a multi-parametric MRI-based tumor habitat imaging biomarker for determining tumor recurrence after SRS for BMs. The primary outcome measure is the time to recurrence, calculated from the date of SRS for BMs until the date of progression assessed according to the Response Assessment in Neuro-Oncology Brain Metastases (RANO-BM) criteria. The timeframe will be restricted to up to 24 months after SRS.

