### SRS treatment

Patients will receive standard SRS treatment as recommended by the neurosurgery team. Participating in this study will not alter the patient’s treatment course in any way.

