### Statistical analysis

Analysis of the association between the tumor habitats and time to recurrence will be conducted using Cox proportional hazards regression analysis. The imaging predictor exhibiting a strong association will be selected on the basis of both univariate and multivariable Cox proportional regression analysis. Adjustments for time-dependent covariates will be made.

The prediction model for time to recurrence will be created by combining imaging predictors and clinical variables. The performance of the prediction model will be analyzed using C-statistics and time-dependent receiver operating characteristic curve analysis, and calibration (Hosmer-Lemeshow goodness-of-fit test) will be evaluated.

The Dice similarity coefficient will be calculated when the recurrence is diagnosed. The area of each habitat before SRS will be divided by the contrast-enhancing lesion at the time of tumor recurrence.

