## Discussion

This study aims to prospectively evaluate a tumor habitat-based imaging biomarker to predict tumor recurrence in SRS-treated BM. Tumor habitat analysis will be conducted using baseline multi-parametric MR images and follow-up MR images captured after SRS treatment. Metastatic tumors are biologically complex and exhibit significant spatial variation in their structural properties. This intratumoral and peritumoral heterogeneity becomes even more complex after SRS, when it becomes combined with radiation-induced changes. The grouping of voxels of similar signal intensity may enable identification of subregions that share common biologic characteristics and respond differently to treatment, providing information that may not be detectable through visual analysis.

A previous autopsy study indicated that the enhancing areas of post-SRS lesions consist of various pathologic components, including viable tumor tissue, necrotic tissue, inflammatory cells, and vessels [22]. The degree of enhancement cannot differentiate between these complex components, and analyses relying solely on enhancing lesions cannot distinguish progression and radiation-induced changes. Previous studies have demonstrated the predictive value of the correspondence or proportion of solid lesions on T2WI and enhancing lesions on CE-T1WI for diagnosing viable tumors [23, 24]. Interval decreases in the ADC or rCBV values of treated lesions have also been reported to indicate tumor responses following SRS [25–28]. However, visual assessment of structural MRI is limited in terms of reproducibility and its inherent subjectivity. Furthermore, a single quantitative parameter may fail to provide a thorough explanation of the intricate tumor biology mixed with RN. Thus, in this study, we will use CE-T1WI and T2WI for the structural tumor habitat analysis, and ADC and CBV maps for the physiologic tumor habitat analysis. The prospective longitudinal analysis of tumor habitats will enable us to track changes across different subregions in fine detail.

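### Discrimination and calibration are assessed only for one model that mixes habitat and clinical predictors, so the plan never shows how much the habitats add

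*Protocol article*

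**What the plan says.** The Primary objective section states: "This study aims to evaluate a multi-parametric MRI-based tumor habitat imaging biomarker for determining tumor recurrence after SRS for BMs". The outcome is time to recurrence by RANO-BM, up to 24 months after SRS.

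The Statistical analysis section has two steps.

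1. Association: "Analysis of the association between the tumor habitats and time to recurrence will be conducted using Cox proportional hazards regression analysis". The imaging predictor with a strong association "will be selected on the basis of both univariate and multivariable Cox proportional regression analysis". The adjusting covariates are not named.
2. Prediction: "The prediction model for time to recurrence will be created by combining imaging predictors and clinical variables". Then "The performance of the prediction model will be analyzed using C-statistics and time-dependent receiver operating characteristic curve analysis". The same sentence goes on to say that "calibration (Hosmer-Lemeshow goodness-of-fit test) will be evaluated".

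The second step refers to one model throughout. The article mentions no model without habitats, no difference in C or AUC, and no test of added value. Its only benchmark is the null AUC of 0.7 under Sample size calculation, which concerns the determination of radiation necrosis (RN).

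Two other places bear on the point. On treatment: "Patients will receive standard SRS treatment as recommended by the neurosurgery team". On the rationale, the Discussion argues that "a single quantitative parameter may fail to provide a thorough explanation of the intricate tumor biology mixed with RN".

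**The concern.** The objective concerns the habitat biomarker, but the performance figures will describe habitats and clinical variables together. In a single-arm cohort, the direct way to see what habitats contribute to prediction is to compare with a model that lacks them. Without it, a good C-statistic could come mostly from the clinical variables, from lesion size, or from overfitting.

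The rationale is also comparative: the Background and Discussion say that combining parameters should do better than simpler measures. A claim of doing better needs something to be better than.

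At stake is how the result is read. The Discussion expects an objective, reliable measure of recurrence to emerge. A respectable C for the combined model would be easy to cite in support, whether or not habitats contributed to it.

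**Working it through.** **1. Is the 0.7 benchmark a habitat-free comparator?** Inputs from Sample size calculation: AUC 0.70 against 0.85, 34 RN and 68 recurrences, alpha 0.05 (taken as two-sided), power 0.80. Hanley-McNeil variance:

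Var(A) = [A(1−A) + (n₁−1)(Q₁−A²) + (n₀−1)(Q₂−A²)] / (n₁n₀), with Q₁ = A/(2−A), Q₂ = 2A²/(1+A), n₁ = 34, n₀ = 68.

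- A = 0.70: [0.21 + 33(0.0485) + 67(0.0865)]/2312 = 0.00329, SE 0.0573.
- A = 0.85: [0.1275 + 33(0.0166) + 67(0.0586)]/2312 = 0.00199, SE 0.0446.
- Power = Φ[(0.15 − 1.96 × 0.0573)/0.0446] = Φ(0.84) = 0.80.

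The plan's 102 cases are reproduced. The calculation tests one AUC against a fixed number, for RN. It compares no two models and does not concern time to recurrence.

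**2. Is there a route to good performance without habitats?** The Progressive disease section requires a 20% increase and at least 5 mm of growth in one lesion. For a patient with a single lesion:

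- 15 mm reference diameter: 5/15 = 33% growth needed.
- 25 mm or more: 5/25 = 20%, so the percentage rule governs.

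Lesion size can therefore influence the outcome by definition. A habitat parameter expressed as a volume would carry size information too.

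**3. Can the combined C tell the cases apart?** Illustration only; every input is assumed. There were 102 patients, exponential event times (mean 20 months at average covariates) and censoring at 24 months only. Two clinical and six habitat variables were independent normals, all forced into the model. Both clinical variables had the stated log hazard ratio (log-HR) per SD; where habitats had an effect, one of the six did. There were 150 runs per row, and 64% to 68% of patients had events. New data means 3,000 fresh patients per run.

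| Clinical log-HR | Habitat log-HR | Combined C | Habitat-free C | Apparent gain | Gain in new data |
|---|---|---|---|---|---|
| 0.4 | 0 | 0.672 | 0.651 | 0.021 | 0.625 − 0.644 = −0.019 |
| 0.7 | 0 | 0.746 | 0.735 | 0.011 | 0.715 − 0.727 = −0.012 |
| 0.9 | 0 | 0.784 | 0.773 | 0.011 | 0.755 − 0.766 = −0.011 |
| 0.4 | 0.5 | 0.707 | 0.641 | 0.066 | 0.669 − 0.632 = 0.037 |
| 0.7 | 0.5 | 0.758 | 0.714 | 0.044 | 0.733 − 0.712 = 0.021 |

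At clinical log-HR 0.7, the combined C is 0.746 without a habitat effect and 0.758 with one. It is highest, 0.784, in a row where habitats do nothing. The gain in new data does separate the cases: negative in all three null rows, positive in both others. The apparent gain is positive even when habitats have no effect, so the gain itself needs optimism correction.

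**The case against.** The strongest reply is that the plan does isolate habitats. Its first analysis is a Cox regression of habitats on time to recurrence, and the Abstract presents that association as the main evaluation. If clinical covariates enter the multivariable model, the test of the habitat terms asks nearly the same question as a likelihood-ratio test. This stands in part. A reader might infer that the study could produce no evidence about habitats at all, or that the model is judged by its C-statistic alone. The documents support neither: the association analyses are planned, and so are time-dependent ROC and calibration. But an adjusted hazard ratio does not measure added discrimination, and the covariates are unnamed.

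The simulation does not follow the plan's selection step. If selection used p < 0.05 with independent candidates (the plan gives no threshold), some null habitat would pass in 1 − 0.95³ = 14% of studies with three candidates and 1 − 0.95⁶ = 26% with six. In most null studies no habitat would be carried forward. This stands, and the table should not be read as a forecast. It does not help where a habitat is selected, because the combined C still gives no share to it.

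A reader might also assume that lesion-mean nCBV and ADC are already computed, that delivered dose is a study variable, or that a particular C value would trigger the biomarker claim. The article says none of these things. It describes nCBV maps and ADC images, from which means could be derived, and sets no C criterion.

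Lastly, this is a condensed article, and a full protocol or SAP may name a comparator. That limits confidence. But the article does set out its performance evaluation, and as written that evaluation measures something other than the stated objective.

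**Conclusion.** The point holds in a limited form. All stated discrimination and calibration results belong to one combined model. The Cox analyses can show association, but nothing stated measures what habitats add to discrimination. The combined model's performance therefore cannot be credited to the habitat biomarker.

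This conclusion rests on the text and not on the simulation, whose effect sizes, event rates and variable counts are assumed. No size of error in the eventual result can be given, and nothing here shows that habitats lack value. It is an inexpensive improvement that should be made, not a flaw that invalidates the study. Confidence is medium, because the fuller documents are not shown.

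**What to change.** In Statistical analysis, prespecify a parsimonious habitat-free reference Cox model. Fit it in the same patients, with the same clinical variables as the combined model plus baseline enhancing-lesion size. Include lesion size in the combined model too, so that the models are nested. Then report:

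- a likelihood-ratio test for the habitat terms;
- the change in C-statistic and in time-dependent AUC, with optimism-corrected bootstrap 95% confidence intervals that repeat the predictor selection in each resample.

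Base the claim about the habitat biomarker on that gain. If the data chose the habitat terms, the likelihood-ratio p-value will be too small, so the bootstrap interval should carry more weight.

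A second comparator with lesion-mean nCBV and ADC, derived from the existing maps, would address the single-parameter argument. It should be optional and depend on the number of events: with the planned 68 recurrences and an assumed 10 to 12 terms, there would be 68/12 = 5.7 to 68/10 = 6.8 events per term.

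The cost is wording and one or two extra model fits, with no new imaging and no effect on patient care. The headline becomes a smaller and less favourable figure.

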### Sample size calculation

The sample size for this prospective study was determined according to binomial receiver operating characteristic curve analysis performed in diagnostic accuracy studies by a biostatistician ([name], with 12 years of experience). The sample size was calculated using PASS 15 Power Analysis and Sample Size (NCSS, Kaysville, Utah, ncss.com/software/pass). The null hypothesis of an area under the curve (AUC) of 0.7 was compared with an alternative hypothesis of an AUC of 0.85 for the tumor habitat analysis for the determination of RN. The target distribution was the rate of RN versus tumor recurrence, which is known to be detected in a 1:2 ratio in post-treatment BM [4]. With an alpha of 0.05 (type-1 error) and a beta of 0.20 (type-2 error), 34 positive cases (RN) and 68 negative cases (tumor recurrence), giving a total of 102 cases, were identified as the appropriate sample size. Considering a dropout rate of 10% and a censoring rate of 20% for BM, 132 patients were found to be appropriate for the study design.

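### The recurrence prediction model has no stated treatment of death before recurrence; if those deaths are censored, its absolute risks exceed the cumulative incidence of recurrence

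*Protocol article*

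**What the plan says.** All statements are in the Methods of the protocol article.

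- **Endpoint (Primary objective).** Time to recurrence is "calculated from the date of SRS for BMs until the date of progression" by RANO-BM. Death is not part of the event. The horizon is fixed: "The timeframe will be restricted to up to 24 months after SRS".
- **Association (Statistical analysis).** The analysis of habitats against time to recurrence "will be conducted using Cox proportional hazards regression analysis".
- **Prediction (Statistical analysis).** "The prediction model for time to recurrence will be created by combining imaging predictors and clinical variables". Its performance "will be analyzed using C-statistics and time-dependent receiver operating characteristic curve analysis", and "calibration (Hosmer-Lemeshow goodness-of-fit test) will be evaluated".
- **Censoring (Sample size calculation).** The only mention is "a censoring rate of 20% for BM". It has no stated cause and serves only to enlarge the sample.

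No section of the article mentions death before recurrence, overall mortality or a competing-risk method.

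**The concern.** With progression as the only event and Cox regression as the method, a patient who dies free of progression is most naturally censored at death. For hazard ratios that is sound: the result is a cause-specific Cox model.

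The plan goes further and builds a prediction model whose calibration will be tested. Calibration needs absolute predicted probabilities and an observed outcome to compare them with. With deaths censored, one minus the Cox survival estimate is the recurrence risk in a setting without death. The recurrence that occurs in real patients is lower, because those who have died cannot recur.

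The two performance measures inherit the problem. A Hosmer-Lemeshow test needs a yes/no recurrence status at a time point, and time-dependent ROC needs cases and controls at a time point. Both require a rule for a patient who dies progression-free at, say, month 8. At stake are the absolute risks attached to the model and the figures by which it will be judged.

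**Working it through.** **The plan's own figures.** The sample size section tests AUC 0.70 against 0.85 for radiation necrosis. A Hanley-McNeil calculation (two-sided alpha 0.05, power 0.80, ratio 1:2) returns 34 + 68 = 102 cases, as stated. The 132 patients match 102 × 1.3 = 132.6, rounded down. These figures reproduce, but they do not concern the prediction model and contain no death or recurrence rate. The inputs below are therefore assumptions.

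**Inputs**
- Horizon: 24 months (Primary objective).
- F: net 24-month recurrence risk, deaths censored. Assumed, 20% to 66.67%.
- D: net 24-month probability of death *without recurrence*. Assumed, 10% to 70%.
- Constant cause-specific hazards. Assumed.

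**Formulas**
- Cumulative hazards over 24 months: H = −ln(1 − F) for recurrence, M = −ln(1 − D) for death without recurrence.
- Cumulative incidence of recurrence: CIF = H/(H + M) × [1 − exp(−(H + M))], where exp(−(H + M)) = (1 − F)(1 − D).

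**Worked case, F = 40% (H = 0.5108)**
- D = 20%: M = 0.2231, so CIF = 0.5108/0.7340 × (1 − 0.60 × 0.80) = 0.696 × 0.52 = 0.362. Ratio 0.40/0.362 = 1.11.
- D = 50%: M = 0.6931, so CIF = 0.5108/1.2040 × (1 − 0.60 × 0.50) = 0.424 × 0.70 = 0.297. Ratio 0.40/0.297 = 1.35.

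**Cumulative incidence over the assumed range**

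| F | D = 10% | D = 20% | D = 50% | D = 70% |
|---|---|---|---|---|
| 20% | 19.0% | 18.0% | 14.6% | 11.9% |
| 40% | 38.1% | 36.2% | 29.7% | 24.4% |
| 50% | 47.7% | 45.4% | 37.5% | 31.1% |
| 66.67% | 63.9% | 61.0% | 51.1% | 42.9% |

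F exceeds the CIF in every cell, by 1 to 24 points. The gap is about 2 to 6 points at D = 20% and about 5 to 16 points at D = 50%.

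**Effect on calibration.** Take F = 40%, correctly estimated with deaths censored. The observed figure depends on where the dead are placed:
- *Counted as non-events:* 36.2% (D = 20%) or 29.7% (D = 50%). The model looks miscalibrated.
- *Dropped:* CIF/(CIF + event-free) = 0.362/(0.362 + 0.48) = 43.0%, or 0.297/(0.297 + 0.30) = 49.7%. The sample is selected on survival and the model looks miscalibrated in the other direction.
- *Censored:* 40% in both cases. The model looks well calibrated, but for the no-death quantity, so the check cannot reveal the gap.

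**Effect on discrimination.** Ranking can change too. From the table, a patient with F = 50% and D = 50% has a CIF of 37.5%, while one with F = 40% and D = 10% has 38.1%. Net risk puts the first patient higher; cumulative incidence puts the second higher.

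**The case against.** The strongest reply is that this argues from silence. The article condenses a fuller protocol, an analysis plan may exist, and censoring rules are commonly left to it. Naming Cox regression does not rule out competing-risk prediction, since cause-specific Cox models can be combined to give cumulative incidence. Nor is net risk an error in itself: if predicted and observed risk both censor deaths, calibration is coherent for net risk, provided death is independent of recurrence given the covariates.

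This stands in part. Censoring at death is implied rather than written, so the point must be conditional. It does not dispose of the point, because the article itself fixes the event, the model and the performance measures, and as written that combination leaves a progression-free death to be censored or miscounted.

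A reader might infer four stronger things that the documents do not support:

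- *That mortality is known to be substantial, so the bias is large.* No mortality figure is given. The 20% censoring rate has no stated cause and cannot be read as a death rate. Overall mortality would be the wrong input anyway, because deaths after recurrence do not compete with it.
- *That an overstated 24-month risk will be published.* Twenty-four months is the outcome timeframe. The article does not promise a 24-month absolute risk; only the calibration step implies absolute probabilities.
- *That the primary association analysis is invalid.* Cause-specific hazard ratios remain valid with deaths censored.
- *That clinical decisions would rest on the inflated risks.* The Discussion ties monitoring and targets to habitat subregions, not to a patient's absolute risk from the model.

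**Conclusion.** The point holds conditionally. If deaths before recurrence are censored and the model's probabilities are read as the chance that recurrence will occur, they are too high at any non-zero mortality. Calibration and time-dependent AUC then either describe a no-death quantity or vary with the handling of the dead.

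The direction is certain under that condition; the size is not. In the illustration, a 40% net risk stands for a cumulative incidence of 36% to 30%, a relative overstatement of about 11% to 35%. This rests on constant hazards and an assumed 20% to 50% net probability of death without recurrence. With D set at 20%, the overstatement is a modest 2 to 6 points across the recurrence risks considered. The habitat hazard ratios stand. The change is worth making before the model is built, but the defect is confined to prediction and its assessment.

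**What to change.** - Keep cause-specific Cox regression for the habitat associations, and state that death without recurrence is censored there.
- For the prediction model, define death without recurrence as a competing event. Derive absolute risk from cause-specific models for recurrence and death combined, or from a Fine-Gray model.
- Report observed recurrence as Aalen-Johansen cumulative incidence.
- Name the prediction horizon. At that horizon, use the competing-risk versions of time-dependent AUC and calibration in place of a Hosmer-Lemeshow test with no rule for patients who died.

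Cost: date of death must be recorded for every patient, there is slightly more analysis work with standard software, and the stated recurrence risks will be lower. Enrolment, imaging and care do not change.

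### The Hosmer-Lemeshow test is named for calibrating a Cox model of censored time to recurrence; it cannot handle patients censored before the horizon, so its result can reflect follow-up loss rather than fit

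*Protocol article*

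**What the plan says.** The outcome is a time to event. Under Primary objective: "The primary outcome measure is the time to recurrence, calculated from the date of SRS for BMs until the date of progression". The same paragraph adds "The timeframe will be restricted to up to 24 months after SRS", so follow-up stops at 24 months.

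Under Statistical analysis, the association between habitats and this outcome "will be conducted using Cox proportional hazards regression analysis", with adjustment for time-dependent covariates. Then: "The prediction model for time to recurrence will be created by combining imaging predictors and clinical variables". Discrimination of that model "will be analyzed using C-statistics and time-dependent receiver operating characteristic curve analysis". For calibration the only method named is "calibration (Hosmer-Lemeshow goodness-of-fit test) will be evaluated". The section gives no horizon for it, no survival version of the test and no rule for patients censored before a horizon.

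Under Sample size calculation, incomplete follow-up is expected: "Considering a dropout rate of 10% and a censoring rate of 20% for BM, 132 patients were found to be appropriate".

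**The concern.** The Hosmer-Lemeshow test groups patients by predicted risk and compares the number of events seen in each group with the number predicted. Both counts presuppose that every patient's status at the horizon is known. A patient censored at, say, 10 months has no known 24-month status. The test can be run only by coding that patient as recurrence-free, which lowers observed risk, or by leaving the patient out. Leaving the patient out raises observed risk, because those who recur early have less time in which to be censored.

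Either way, the gap between observed and predicted risk is partly produced by follow-up loss. Calibration is what supports statements about a patient's absolute risk. The Discussion expects the biomarker to be reliable enough to separate areas needing close monitoring from areas that can be observed. A calibration statement that shifts with dropout is weak support for that.

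The problem is confined to one clause. The discrimination measures in the same sentence include a time-dependent method, and the Cox model itself handles censoring.

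**Working it through.** **What the plan itself computes.** The plan gives no figure for calibration. Its one calculated figure, 102 evaluable cases, reproduces as 34 + 68 for a test of AUC 0.70 against 0.85 (Hanley-McNeil variance, two-sided 5%, 80% power). It has no bearing on calibration.

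**Inputs.**
- From the protocol: 132 patients, 10% dropout, 20% censoring, 24-month limit.
- Number analysed: 132 × 0.90 = 118.8, taken as 119.
- Assumed: 20% of patients actually censored before recurrence or 24 months, independently of outcome.
- Assumed: exponential recurrence times with a log hazard ratio of 0.7 per SD of one predictor.
- Assumed: the 24-month recurrence rate, which the documents do not give, so it is varied.

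**Statistic.** With G = 10 risk groups, observed events O, expected events E and group size n:

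χ² = Σ (O − E)² / [E(1 − E/n)]

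The predictions are the true 24-month risks, so calibration is perfect. The reference distribution is chi-square with 10 degrees of freedom, and a sound test rejects in about 5% of runs. With no censoring, at 0.025 recurrences per month (47% by 24 months), rejection was 4.5%.

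**Result with 20% censored early and counted as recurrence-free.**

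| Assumed 24-month recurrence | False rejection (nominal 5%) |
|---|---|
| 26% | about 4% |
| 34% | about 5% |
| 47% | about 15% |
| 61% | about 41% |

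Observed/expected is about 0.87 to 0.89 across these settings. If the censored patients are dropped instead, it is about 1.07 to 1.09.

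**Why the ratio is stable and the rejection rate is not.** The ratio translates into a number of missing events that grows with the event rate:
- 26% recurrence: 119 × 0.26 = 30.9 expected events; 30.9 × (1 − 0.89) = about 3.4 missing, too few for the test to detect.
- 61% recurrence: 119 × 0.61 = 72.6 expected events; 72.6 × (1 − 0.87) = about 9.4 missing.

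**Effect of the amount of early censoring.** At 47% recurrence, with 20%, 30% and 40% of patients actually censored early, false rejection is about 15%, 29% and 53%.

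**Second design.** Here a correctly specified Cox model with three predictors was fitted to 132 patients (Hosmer-Lemeshow with 10 groups and 8 degrees of freedom; 800 runs per setting). With 20% censored early:

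| Recurrence | Coding of censored | Observed vs predicted | Ratio | False rejection |
|---|---|---|---|---|
| 30% | recurrence-free | 26.6% vs 29.8% | 0.89 | about 7% |
| 30% | dropped | 33.4% vs 30.6% | 1.09 | about 7% |
| 50% | recurrence-free | 43.9% vs 49.5% | 0.89 | about 28% |
| 50% | dropped | 54.9% vs 51.1% | 1.07 | about 4% |

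The bias is the same size as in the first design. A comparison against Kaplan-Meier observed risk in five groups (Greenwood-Nam-D'Agostino) rejected in 5% to 7% of runs for fitted models, from no early censoring up to 30%.

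**The case against.** **The size is not known.** The protocol gives no recurrence rate. Its 20% is a sample-size allowance and may include patients who are recurrence-free at 24 months. Those patients have a known 24-month status and cause no bias at that horizon. This stands: the figures above are conditional and must be shown as a range.

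**A reader might infer that the test will reach the wrong verdict.** The documents do not support that. At 26% to 34% recurrence, with 20% censored early, false rejection is about 4% to 5%. When the censored are dropped it is only about 4% to 7% in the fitted-model check. What persists is the bias in observed against expected risk.

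**A reader might also infer that a poorly calibrated model would pass, or that deaths without recurrence make the test worse.** Neither was examined. A patient who dies without recurrence has a known status of no recurrence. Any mismatch there comes from a Cox prediction that treats death as censoring, not from Hosmer-Lemeshow.

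**The authors may mean a survival extension of the test.** That is possible in a condensed article, but the text names the standard test without qualification. If an extension is meant, saying so and giving the horizon settles the point.

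**Calibration is not a stated objective and does not drive the sample size.** This is true, and it limits the weight of the point. It does not make it a detail left to the analysis plan, because the protocol names a method and the named method does not fit the outcome.

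**Conclusion.** The point holds as a badly fixed choice of method. The protocol names a binary-outcome test for a model whose outcome it expects to be censored, so the calibration result can reflect loss to follow-up rather than fit. If 20% of about 119 patients are censored before recurrence or 24 months, observed risk is understated by roughly 11% to 13%, or overstated by roughly 7% to 9%, depending on how they are handled. Inflation of the test's false-rejection rate ranges from none to severe with the unstated recurrence rate. These sizes rest on independent censoring, exponential times and the assumption that all 20% are lost early; less early loss means less bias. The Cox analysis of habitats and time to recurrence, and the time-dependent ROC analysis, are not affected.

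**What to change.** In Statistical analysis, replace the Hosmer-Lemeshow test with calibration at stated horizons, for example 12 and 24 months. Compare mean predicted risk with Kaplan-Meier observed risk by risk group, and report a calibration plot and calibration slope. If a test is wanted, use Greenwood-Nam-D'Agostino with few groups, and let the plot and slope carry the conclusion. With known true risks and five groups in 132 patients, that test itself rejected in about 9% to 13% of runs, even though it held 5% to 7% for fitted models.

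Two conditions belong in the same text:
- **Competing death.** If death without recurrence is treated as a competing event, predicted and observed risk must both be cumulative incidences (Aalen-Johansen for the observed side). Mixing the two creates apparent overprediction. With assumed hazards of 0.025 per month for recurrence and 0.01 for death, Cox-type risk at 24 months is 1 − exp(−0.025 × 24) = 45%. The cumulative incidence is (0.025/0.035) × [1 − exp(−0.035 × 24)] = 41%.
- **Time-dependent covariates.** These do not directly define a risk at a fixed horizon. Compute the predictions from baseline predictors only, or from a stated landmark time.

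The cost is a few sentences and a small amount of extra analysis in standard software. No data collection changes.
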